## **2. Adequacy Of Protection Against Risks**

### **2.A. Recruitment and Informed Consent**

Recruitment: Prior to recruitment, the OHSU IRB will approve this study for human study. The study will recruit from the NIA-Layton Aging and Alzheimer’s Disease Center at OHSU, which serves the entire state of Oregon. The study will be advertised in local retirement communities, newspapers, radio, television, and the NIH Clinical Trials website with associated press release. A blinded scan of the OHSU clinical database determines how many potential participants have visited OHSU in the last year. A recent scan that included people meeting our inclusion criteria, including: age 80 and older who have visited the academic medical center within the past year, without a diagnosis of a dementing illness, free of contraindications for MRI

(pacemaker), without ventricular-tachycardia, ventricular fibrillation, IDDM, cancer and residence within close proximity to OHSU (Oregon and Washington counties close to Portland and Bend), Oregon (counties include Multnomah, Clark, Clackamas, Washington, Columbia, Polk, Marion, Deschutes) identified 6,571 eligible men and women for recruitment. Assuming 20% of this population has no evidence of WMH and plasma pufas too high then that leaves 5,256 elders. We would need to recruit <3% of this population to satisfy our recruitment goals. **Individuals identified through medical record scans will be sent an IRB approved letter describing their potential eligibility for the study. We will also utilize NeuroNext database of people that have consented to be contacted about clinical trial opportunities at OHSU.** In addition, the NIA-Layton Aging & Alzheimer's Disease Center maintains direct contact for its ongoing longitudinal aging studies in over 50 aging centers, retirement communities and community organizations in the Portland metro area. To compensate for cost of travel, time and effort each participant will receive \$40/complete visit to OHSU. **Individuals who complete a combined visit 1 and 2 will receive \$80 for their first visit and \$40 for any subsequent visits.** Participants traveling to OHSU for MRI scan from the > 100 miles outside of Portland will be compensated at \$200 for each visit to OHSU for gas and overnight lodging costs.

**Informed Consent:** Prior to the in-clinic screening visit, all potential participants and their study partners will be mailed a copy of the IRB approved consent/HIPAA authorization form so that they may be fully informed of all aspects of their participation in the study. At the time of consent one of the study investigators, coordinators, or the research assistants will review the consent/HIPAA authorization form and then will ask the participant and study partner to describe key points in the consent form (e.g. purpose of study, knowledge of placebo control group, length of study) before the consent form will be signed. Once the participant signs the consent form he or she will continue with screening assessments.

## **2.B. Protection Against Risk**

All information about subjects will be locked so that only authorized study staff will have access. Research records will be coded with a unique patient identification number; therefore will contain no personal identifiers. All records with identifying information will be locked so that only authorized study staff will have access to them. Data will be kept in locked cabinets separate from identifiers. Computer files will be password protected. No one other than the researchers will have access to identifiable data. Participants will be told that they have the right to refuse to answer any question(s). If they are upset by a question they will be referred to the Principal Investigator. We will monitor adverse events by laboratory tests, which include prothrombin time (PT/INR), CBC and CMP and by every 3-month adverse events report. We are monitoring the effects of treatment on CBC and CMP at baseline, 3, 6, 12, 18, 24 and 36-months. Subjects whose labs reflect significant abnormalities, at 3 months (that have not reported adverse events) will be further screened to determine the potential cause(s) of the lab abnormalities; if the study treatments are suspected, we will discontinue treatment and remove the subject from the study. A data safety monitoring board (DSMB) will convene biannually to study unblinded data on AE coded by organ system. All subjects will be given a telephone number and be instructed to call [name] or the trial coordinator if they believe they are experiencing severe side effects from the study medication.

Plan for informing participants and their caretakers of incidental findings with potential significance from MRI: The MRI derived from this study will be reviewed for clinically relevant findings that would impact health (i.e., cortical stroke, tumor, normal pressure hydrocephalus). If clinically relevant findings are identified, [name] or [name] will contact a neuroradiologist for a clinical read within 78 hours of identified finding.. The PI or study coordinator will notify the subject by phone within one week of the discovery to discuss the abnormal finding. The subject's PCP will be notified of the finding and the clinical brain scan will be provided to support subject the appropriate care.. [name] (sitePI) will also work with the PCP to facilitate an expedited referral to a specialist (e.g., neurologist, neuroradiologist) if the PCP deems necessary.

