  - g. Anticoagulation therapy: Vitamin K antagonist: warfarin (Coumadin, jantoven), Factor Xa inhibitors: rivaroxaban (xarelto), fondaparinux (arixtra), dabigatran (pradaxa), apixaban (eliquis); Low molecular weight heparins: dalteparin (fragmin), enoxaparin (lovenox)(Incident use of anticoagulant therapy will exclude further study drug allocation. However, subjects will be asked to complete all follow-up visits.)

**Study Supplement and Dose.** Because neuronal functioning is dependent on DHA  and EPA may have vascular effects , we have elected to use a combination supplement. Since these pufas also exist together in nature, this form of supplementation will be less likely to create an unfavorable imbalance in fatty acid metabolism compared to a single constituent form, especially during long-term use in an older population. The form and daily dose of EPA and DHA was chosen because it is a form used in a previous randomized, double-blind, placebo-controlled study in elders with mild to moderate AD (Table 5). This dose was able to significantly increase both EPA and DHA levels in RBC membranes at 6 and 12 months in study participants randomized to receive fish oil (n=13 at both time points), and was associated with an excellent safety profile (Figure and Table 6). This dose also penetrates the threshold plasma levels associated with neuroprotection in our preliminary and published studies. The study supplement will contain one of the following and all study supplements will be taken with meals: 1) Each ProOmega 3 (Nordic Naturals) soft gel contains 1 gram of fish oil concentrate guaranteed to have a concentration of long-chain omega 3 fatty acid ethyl esters at 70%, primarily EPA (325 mg/g) and DHA (225 mg/g). Three capsules is the daily dose, which will provide a total of 1650 mg of omega 3 pufas (975 mg EPA + 675 mg DHA) per day; 2) Placebo oil contains soybean oil.

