**Adverse events.** Adverse events will be monitored in “real time” with weekly review of AE’s with study staff using clinical judgment to determine reporting to IRB and FDA. An external data safety monitoring board (DSMB) will convene biannually to study unblinded data on AE coded by organ system. Although assessment of AEs will also include solicitation of non-specific change (e.g., “do you feel different since beginning the treatment?”), a 12-item AE checklist covering all major organ systems will be included to probe for AEs. The nature of each AE, its severity (mild, moderate, or severe), its likely relationship to study treatment (definite, probable, possible, not related, or unknown), its duration, and any necessary treatment modifications or adjustments will be recorded. In addition to the monitoring and recording of AEs at each 3 month subject contact, labs to assess basic metabolic function (including liver function tests), CBC and PT/INR are performed at screening and at months 6, 12, 18, 24 and 36. Incident use of oral anticoagulant therapy is identified through subject interview that occurs every 3 months. Incident anticoagulation therapy cases are asked to stop the supplement and complete complete the remaining follow up visits. Participants will be reminded and encouraged during clinic visits and phone checks to contact the study coordinator or investigator if a moderate or serious AE occurs.

**Compliance:** Compliance will be measured in-clinic by pill count. In addition to the in-clinic checks on compliance, each subject will receive a phone call to check on compliance every 3 months. If a subject’s compliance drops < 80% at any time, they will be contacted by the trial coordinator by phone to find out why

and to aid the subject in finding ways to increase compliance. Although plasma fatty acid measurement is an independent measure of compliance, knowing the results of fatty acids levels during the study would un-blind the study. Plasma PUFA index will be used during data analysis to corroborate pill count.

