**Analytic approach.** First we will conduct univariate analyses using changes in WMH progression (**Aim 1**), ICAM-1 (**Aim 2**), and cognitive test scores (**Aim 3**) between baseline and three follow-up assessments (baseline, 12, 24 and 36 month) for WMH, ICAM, and cognitive outcomes with a predictor variable being pufas active vs. placebo. Student's t-test will be used for this descriptive analysis based on ITT. Next we apply linear mixed effects multiple regression models with longitudinal WMH progression (**Aim 1**), sICAM-1 (**Aim 2**), and cognitive test scores (**Aim 3**) as outcomes, a main predictor variable as a dummy variable for pufas (active vs. placebo as a reference) and its interaction with a time variable. Control variables include age at baseline, sex, past history and incidence of vascular diseases including hypertension, ApoE4 allele and depression. Intercept and time variables in years (years from baseline) are treated as random effects in all models. We will use an unstructured error covariance structure and estimate parameters using restricted maximum likelihood procedures. Missing data points in the analytical sample are considered missing at random^69 and the above approach is adequate under this assumption. Interaction term between the pufa and placebo groups and time is of our substantive interest. That is, we are interested in examining the magnitude and significance of the difference in time slopes between the active and placebo groups. In all models quadratic and higher order time variables will be included if it improves the model fitness. The overall fit of the models will be examined using a combination of formal fit criteria and visual inspection of residual plots. Results will be considered significant at  $p < 0.05$ , but we will also provide Bonferroni-adjusted p-values to correct for multiple statistical tests.

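### The month-3 laboratory rule removes participants from the study when treatment is stopped, while anticoagulant stoppers stay in follow-up; this weakens the ITT comparison and should be reconciled

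*Protocol*

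**What the plan says.** Section 2.B sets a rule for one group: "Subjects whose labs reflect significant abnormalities, at 3 months (that have not reported adverse events) will be further screened" for the cause. It continues: "if the study treatments are suspected, we will discontinue treatment and remove the subject from the study".

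For another reason to stop, the protocol keeps the participant in follow-up. Exclusion criterion 14g bars further study drug after incident anticoagulant use and adds "However, subjects will be asked to complete all follow-up visits". The Adverse events paragraph agrees: "Incident anticoagulation therapy cases are asked to stop the supplement and complete complete the remaining follow up visits".

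The Analytic approach paragraph attaches intention-to-treat to the descriptive t-tests. It makes the treatment-by-time interaction of the mixed models the contrast of main interest, and says "Missing data points in the analytical sample are considered missing at random".

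The sections also disagree on the laboratory schedule. Section 2.B says "We are monitoring the effects of treatment on CBC and CMP at baseline, 3, 6, 12, 18, 24 and 36-months". The Adverse events paragraph says "CBC and PT/INR are performed at screening and at months 6, 12, 18, 24 and 36". Table 7, the Safety labs paragraph, sections 1.B and 1.C, and the Data and Safety Monitoring Plan likewise show no month-3 safety laboratory test.

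**The concern.** The protocol recognises that stopping the supplement need not end outcome collection, but applies this to one route of stopping and not the other, and gives no reason for the difference.

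Timing makes this matter. The rule is tied to month 3, and WMH and cognition are first remeasured at month 12. A participant removed at that point has a baseline scan and no observed change. Data collection ends because treatment is suspected of causing an abnormality, so the missing values may be related to treatment. Blood count and metabolic results are not among the listed control variables (age, sex, past and incident vascular disease, ApoE4, depression), so the model does not condition on what led to the removal.

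At stake is avoidable bias in the WMH slope difference. An analysis plan can model missing values, but it cannot recover scans that were never taken.

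**Working it through.** **1. The two routes side by side**

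| | Suspected treatment-related laboratory abnormality at month 3 (section 2.B) | Incident anticoagulant (criterion 14g; Adverse events) |
|---|---|---|
| Supplement | stopped | stopped |
| Outcome follow-up | removed from study | asked to complete remaining visits |
| Follow-up MRI and cognition | none | months 12, 24, 36 as far as still due |

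The month-3 blood sample may exist for sICAM-1, so the complete loss concerns WMH and cognition (Aims 1 and 3).

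**2. The plan's own sample size (Table 8)**

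Inputs: difference 2.8 cc (7.0 minus 4.2), SD 5.0, two-sided alpha 0.05, power 80%.

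- n per arm = 2 × (1.960 + 0.842)² × 5.0² / 2.8² = 50.1, or 51 rounded up. The plan states 50, where power is 79.96% by the normal approximation. The figure reproduces.
- With 30% attrition, 150 × 0.70 / 2 = 52.5 per arm. The SE of the difference is 5 × √(2/52.5) = 0.98 cc.

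**3. Size of a possible bias**

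The protocol gives no removal rate, so a range is assumed. Let a share f of the active arm be removed and none of placebo, and let the removed differ from the retained by g cc in 3-year change. The full-arm mean is then the retained mean plus f × g, so an analysis that recovers nothing is off by f × g. Power is Φ(2.8/SE − 1.96), with SE = 5 × √(1/52.5 + 1/(52.5 × (1 − f))).

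| f (of 75) | Bias, g = 2.8 cc | % of 2.8 | Bias, g = 5 cc (1 SD) | % of 2.8 | Power |
|---|---|---|---|---|---|
| 1% (about 1) | 0.028 cc | 1.0% | 0.05 cc | 1.8% | 81.7% |
| 2% (1.5) | 0.056 cc | 2.0% | 0.10 cc | 3.6% | 81.4% |
| 5% (about 4) | 0.14 cc | 5.0% | 0.25 cc | 8.9% | 80.8% |
| 10% (7.5) | 0.28 cc | 10.0% | 0.50 cc | 17.9% | 79.7% |

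If those removed would have progressed faster, the error favours active treatment; if slower, it goes against it. With removal in both arms the bias is the difference of the two products, f × g in active minus f × g in placebo, and it cancels if these are equal.

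**4. Information lost**

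Losing a share f of one arm leaves 2(1 − f)/(2 − f) of the information. For f = 1% this is 1.98/1.99 = 0.995, a loss of about 0.5%.

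**The case against.** The case for leaving the text alone has several sound parts.

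- **Scope.** The rule covers abnormalities at month 3 in participants without reported adverse events, after a search for the cause. A reader might infer that every laboratory-related stop ends participation. The text sets no such rule for later visits or for adverse-event stops in general.
- **The trigger may seldom or never occur.** If Table 7 is followed, there is no month-3 safety result to act on. This stands, but it shows a second contradiction in section 2.B rather than excusing the first.
- **Both arms, blinded.** Suspicion is formed without knowledge of assignment, so placebo participants can also be removed. The pilot reports no significant difference between groups in adverse events, though with only 13 per arm. Nothing in the protocol shows that removal would differ by arm.
- **The model is not helpless.** Baseline WMH is part of the longitudinal outcome, and the protocol names WMH volume and age as strong predictors of progression. Vascular history and incidence are adjusted for. Missing at random is therefore strained for these participants, not refuted. Sensitivity analyses may stand in an analysis plan that is not at hand.
- **Attrition.** Nothing shows that these removals come on top of the 30% allowance.

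One could also say that removal is loose wording for stopping the capsules. That does not stand: the sentence names stopping treatment and removal from the study as two acts.

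**Conclusion.** The inconsistency is real. Section 2.B ends outcome follow-up for one kind of treatment stop, while criterion 14g and the Adverse events paragraph continue it for another. A participant removed around month 3 supplies no follow-up WMH or cognitive value, for a reason that may be related to treatment and lies outside the model covariates. This weakens the intention-to-treat comparison and strains the missing-at-random assumption.

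A reader might go further and infer that the intention-to-treat comparison is broken. The protocol does not support that: it gives no removal rate, the rule is narrow and applies blinded to both arms, and data collected before removal are available to the mixed model. The bias of about 2% to 18% of the 2.8 cc target rests on three assumptions: removal of 1% to 10% of the active arm, none in placebo, and a 1 SD gap. At its upper end, 0.50 cc is about half of one standard error (0.98 cc). Power barely moves. The reason to act is that the lost scans cannot be recovered and the correction is cheap, not that a large bias has been shown.

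**What to change.** Leave the decision to stop treatment as it is. In section 2.B, replace the removal clause with a request that the participant complete all remaining visits, including annual MRI, blood sampling and cognitive testing, in line with criterion 14g and the Adverse events paragraph. State that these data enter the intention-to-treat analysis.

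Separately, reconcile the month-3 laboratory test in section 2.B with Table 7, the Adverse events and Safety labs paragraphs, sections 1.B and 1.C, and the Data and Safety Monitoring Plan. Which schedule is intended is for the investigators to say.

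The cost is an amendment to the wording and a small number of additional retained visits, with at most three annual MRI scans per participant concerned. The protocol shows no budget, and its timeline foresees 110 participants at the end (150 − 15 − 14 − 11), so these visits should be counted as a small extra cost rather than assumed to be already funded.

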## **3. Potential Benefits Of The Proposed Research To The Subjects And Others**

PUFAs have demonstrated anti-inflammatory, and more specifically, anti-leukocyte migration properties. They may have potential benefit for chronic disorders that have an inflammatory component. PUFAs have also been reported to decrease triglyceride levels, blood pressure and reduce cardiac related mortality so this therapy may be beneficial to subjects that are at risk for vascular disease.

## **4. Importance Of Knowledge To Be Gained**

This study will test the safety and effectiveness of pufas in favorably modifying vascular contributions to cognitive decline in non-demented elders. Because there are no current therapies that prevent age-related cognitive decline, it is an important public health issue to scientifically evaluate this therapy and learn the potential for risk reduction.

## 5. Data And Safety Monitoring Plan

Adverse events will be monitored in “real time” with weekly review of AEs with study staff using clinical judgment to determine reporting to IRB and FDA. A data safety monitoring board (DSMB) will convene biannually to study unblinded data on AE coded by organ system. Although assessment of AEs will also include solicitation of non-specific change (e.g., “do you feel different since beginning the treatment?”), a 12-item AE checklist covering all major organ systems will be included to probe for AEs. The nature of each AE, its severity (mild, moderate, or severe), its likely relationship to study treatment (definite, probable, possible, not related, or unknown), its duration, and any necessary treatment modifications or adjustments will be recorded. In addition to the monitoring and recording of AEs, labs to assess basic metabolic function (including liver function tests), CBC and prothrombin time will be performed at screening and months 6, 12, 18, 24 and 36. Participants will be reminded and encouraged during clinic visits and phone checks to contact the study coordinator or investigator if a moderate or serious AE occurs.

